## Abstract

**Background:**

Opioid dependence has devastating and increasingly widespread consequences and costs, and the most common outcome of treatment is early relapse. People who inject opioids are also at disproportionate risk for contracting the human immunodeficiency virus (HIV) and hepatitis C virus (HCV). This study tests an approach that has been shown to improve recovery rates: medication along with other supportive services (medication-assisted treatment, or MAT) against MAT combined with a smartphone innovation called A-CHESS (MAT + A-CHESS).

**Methods/design:**

This unblinded study will randomly assign 440 patients to receive MAT + A-CHESS or MAT alone. Eligible patients will meet criteria for having an opioid use disorder of at least moderate severity and will be taking methadone, injectable naltrexone, or buprenorphine. Patients with A-CHESS will have smartphones for 16 months; all patients will be followed for 24 months. The primary outcome is the difference between patients in the two arms in percentage of days using illicit opioids during the 24-month intervention. Secondary outcomes are differences between patients receiving MAT + A-CHESS versus MAT in other substance use, quality of life, retention in treatment, health service use, and, related to HIV and HCV, screening and testing rates, medication adherence, risk behaviors, and links to care. We will also examine mediators and moderators of the effects of MAT + A-CHESS.

We will measure variables at baseline and months 4, 8, 12, 16, 20, and 24. At each point, patients will respond to a 20- to 30-min phone survey; urine screens will be collected at baseline and up to twice a month thereafter. We will use mixed-effects to evaluate the primary and secondary outcomes, with baseline scores functioning as covariates, treatment condition as a between-subject factor, and the outcomes reflecting scores for a given assessment at the six time points. Separate analyses will be conducted for each outcome.

**Discussion:**

A-CHESS has been shown to improve recovery for people with alcohol dependence. It offers an adaptive and extensive menu of services and can attend to patients nearly as constantly as addiction does. This suggests the possibility of increasing both the effectiveness of, and access to, treatment for opioid dependence.

**Trial registration:**

ClinicalTrials.gov, NCT02712034. Registered on 14 March 2016.

**Electronic supplementary material:**

The online version of this article (doi:10.1186/s13063-016-1726-1) contains supplementary material, which is available to authorized users.

## Background

Opioid dependence has devastating consequences for patients, family members, and communities. In 2012, an estimated 2.1 million Americans had opioid use disorders (OUDs) related to prescription opioids, and 467,000 had OUDs related to heroin [1]. The total volume of opioids prescribed in the health care system has risen steeply in recent years. In 1991, about 76 million prescriptions were written for opioids; in 2013, about 207 million prescriptions were written [2]. A growing proportion of people with OUDs started their use of opioids by taking prescription opioids. Emergency department visits related to the nonmedical use of opioids rose from 144,600 in 2004 to 305,900 in 2007 [3] and unintentional overdose deaths from opioids have more than quadrupled since 1999, reaching their highest level ever in 2014 [2, 4]. OUDs also have been a primary driver of the increased spread of human immunodeficiency virus (HIV) and hepatitis C virus (HCV) in many rural and suburban communities in the US [5, 6].

Existing treatments for OUDs often fail. Following detoxification from opioid dependence, early relapse is the most common outcome [7]. After inpatient treatment, the vast majority of patients relapse within a year, often within the first few months [8]. Medication-assisted treatment (MAT) arose when methadone became available in the 1960s. Along with other supportive services, such as peer support, MAT has been shown to increase rates of recovery from OUD [9]. Yet those who receive MAT still do not generally maintain long-term abstinence [8, 10].

Access to treatment is an enormous challenge, with only 10.7% of OUD patients who needed treatment in 2012 receiving it [11]. Effective treatment is complex and demanding because OUDs are chronic diseases that require ongoing medication, behavioral counseling, and overdose protection, as well as screening and treatment for infectious disease and comorbid psychiatric disease [2]. Effective treatment is also complex because affected populations differ in the etiology and course of their addiction, motivation for treatment, and reasons for relapse, including notable differences between men and women [12]. For example, women tend to progress more quickly from the start of substance use to the start of dependence, have a higher rate of cooccurring mood and anxiety disorders, and have better outcomes on buprenorphine than on methadone [12]. Finally, retention in treatment, which is known to reduce drug use [13], remains a challenge in treating OUDs [14–19]—so much so that treatment retention is often itself regarded as a desired outcome [20].

Testing and links to care for HIV and HCV are essential for people who inject opioids. Those who inject drugs are at greater risk of contracting HIV and are less successfully linked to [21–23] and retained in [24–26] clinical care. Antiretroviral therapy is recommended for all patients living with HIV, but treatment is under-used [27] and often suboptimally effective [23, 28] among people who inject drugs. HCV occurs primarily in people who inject drugs, with 90% of older injection-drug users infected [29–31]. HCV is the most common blood-borne infection in the US [32] and the most common cause of end-stage liver disease and the need for liver transplants.

The randomized clinical trial described here assesses the extent to which the considerable challenges of effectively treating OUDs can be addressed by an mHealth intervention. Specifically, we pair MAT with a smartphone-based innovation called Addiction CHESS (A-CHESS). A large (*n* = 349) randomized controlled trial (RCT) previously found that A-CHESS decreased risky drinking days and enhanced long-term abstinence among alcohol-dependent people leaving residential treatment, one third of whom reported illicit opioid use [33]. Related field tests in the Veterans Administration and drug courts and among pregnant women in Appalachia [34] also found a positive impact on alcohol and opioid abuse of providing smartphones with A-CHESS. In this trial, we assess the potential of A-CHESS to improve long-term outcomes of MAT among OUD patients. Furthermore, the study seeks to understand—through analyses of mediators and moderators and exploratory analyses—the ways in which A-CHESS works and does not work, for whom, and under what circumstances. Our research team has also developed and pilot-tested systems for improving engagement in care for patients with HIV and improving testing and links to care for patients with HCV. For the present study, these innovations related to HIV and HCV have been incorporated into A-CHESS, allowing us to evaluate whether A-CHESS can also improve screening and treatment outcomes for these conditions.

## Methods/design

### Study design, hypotheses, and outcomes

The study, a RCT, will assign 440 opioid users from three addiction treatment centers to receive either MAT + A-CHESS or MAT alone. Patients will be followed for 24 months. The primary hypothesis is that participants assigned to MAT + A-CHESS will have, compared with a control group, a lower percentage of days using illicit opioids. Secondary hypotheses are that those assigned to MAT + A-CHESS will have, compared to the control group, less use of other nonprescribed substances, higher quality of life, greater retention in treatment, and lower health service use. Secondary hypotheses related to HIV/HCV are that those assigned to MAT + A-CHESS will have higher screening and testing rates, greater medication adherence, fewer risk behaviors, and better linkage to care (i.e., referrals that result in in-person visits with providers). We also hypothesize that autonomy (or intrinsic motivation), competence, and relatedness [35] will mediate the effect of MAT + A-CHESS, along with negative affect and self-stigma. We will also determine the person-level factors that moderate the impact of MAT + A-CHESS versus MAT alone (e.g., gender, SUD severity, pain severity, severity of withdrawal symptoms, and loneliness). For patients receiving MAT + A-CHESS, we will examine whether patterns of using A-CHESS and communication style within peer discussion forums are predictors of study outcomes [36]. Figure 1 shows the logic and outcomes for the project. We will use quantitative and qualitative analyses to examine long-term impact, with survey data collected every 4 months during the 24-month period.

**Fig. 1 Fig1:**
[figure not shown]
Logic and outcomes of the study

### Interventions

#### Control condition: MAT

Patients in the control condition will receive treatment as usual including MAT. Treatment could consist of a recovery plan, medication, and regularly scheduled behavioral interventions such as monthly group counseling sessions, sessions with a substance abuse counselor, and Narcotics Anonymous/Alcoholics Anonymous (NA/AA) meetings. Medication may include methadone, injectable naltrexone, or buprenorphine. The sequence and duration of medication and behavioral interventions will vary by patient and site. Discussions with sites revealed that we should not try to control variations because they are tailored to individual patients. We will document which medications are used and will include as covariates when and how medications change between the 4-month surveys.

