Coach-monitored discussion groups [44] foster the exchange of emotional, informational, and instrumental support among patients. Discussions are monitored daily by an A-CHESS coach to encourage appropriate use. Coaches are not counselors, but are members of the research team trained on A-CHESS, risk identification, referral, and technology-based patient engagement. They are skilled in constructive interaction and persistence and are willing to work unusual hours. The coaches encourage individuals to follow up with their health care providers/prescribers regarding medication-assisted treatment questions. We found that a coach increases and sustains use of A-CHESS [45]. Every week, a coach reviews use data. Based on what the coach sees, they write messages to the participants. For example, (1) to a patient active on A-CHESS, “Hi [name], Just wanted to say hello and see how things are going. Looks like you are doing a great job of recovery and tracking, which is wonderful. Let me know if there is anything I can help with. Take care and keep it up! [name].” and (2) to a patient who is not logging in: “Hi [name], Just checking in to see how you are coming with your recovery goals. You have not logged in for a while so I figured I would say hi. Take care and let me know what I can do to help! [name].”

Possible counselor alerts. A-CHESS sends an email notification to an A-CHESS coach if a patient reports substance use or is over a preset risk threshold on self-monitoring items. The coach may alert a counselor or encourage the patient to seek further support within A-CHESS (e.g., by using discussion groups, games, and relaxation exercises; revisiting their personal recovery motivation; or listening to personal stories from others in recovery) or recommend that the patient seek other professional help.

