### Randomization

The project director will use a computer-generated allocation sequence to randomize participants in a 1:1 ratio to MAT + A-CHESS or MAT alone, stratifying on gender and site and balancing on age, level of care (intensive outpatient treatment, day treatment, or weekly or monthly counseling), and whether patients had prior SUD treatment. The project director will inform the site coordinator of the group assignment by email; in the email, the participant will be identified only by study ID (the code used to make the identity of participants unknown). The site coordinator will initiate patients into the study condition and, if the patient is assigned to MAT + A-CHESS, provide training.

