Missing data. In previous addiction work, we completed 85% of surveys at 4, 8, and 12 months. We anticipate greater reductions at months 16, 20, and 24, reaching about 65% by month 24. In previous studies, we have kept missing data on core items in a survey to about 2% and expect a comparable rate in this study. In addiction treatment, data are not likely to be missing at random (i.e., the probability that data are missing is related to what the data would have been had the data been observed). For example, some patients may not want to disclose opioid use in surveys. Because this may lead to biased parameter estimates for our models, we will identify missing data patterns and use pattern-mixture modeling to test the sensitivity of our longitudinal intervention analysis to missing data assumptions [74–77] and conduct other sensitivity analyses after imputing missing data with a range of clinically plausible values based on explicit assumptions for the missing data (e.g., best-case, worst-case; with and without multiple imputation) [78–80].

Intention-to-treat and subject noncompliance. Standard intention-to-treat (ITT) estimates the average treatment effect by comparing outcomes based on assignment to treatment, but ignoring use of the treatment. Because ITT estimates do not represent treatment efficacy under noncompliance (e.g., a patient is randomized to A-CHESS but does not use the system), we will address noncompliance by also estimating treatment effects only for compliers using as-treated, per-protocol [81], and CACE (Complier Average Causal Effect) [82].

Dropout rates. In our A-CHESS RCT with alcohol-dependent patients [33], 88 patients were using opioids as well as alcohol; 261 were not using opioids. We compared the post-test survey response rate of opioid-using patients to the response rate of patients who did not use opioids. The non-opioid-using patients’ response rates were 94.3% at 4 months; 90.6% at 8 months, and 86.7% at 12 months. The opioid-using patients’ response rates were 91.2%, 86%, and 79.1%. Response rates declined in a relatively linear fashion in both groups, with reductions of about 5 percentage points in each period. We assumed a 65% response rate at 24 months by continuing the drop off rate for each of the three periods from 79% to 74% to 69% to 64%. Hence, we believe it is likely that by the end of the study we will still be able to reach 65% of patients originally enrolled.

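### The protocol plans to adjust for medication changes that occur after randomisation, without limiting this to secondary or sensitivity analyses; in the outcome models this may move the estimate away from the intention-to-treat effect

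*Protocol article*

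**What the plan says.** Under Control condition: MAT, the protocol article explains that medication is deliberately left uncontrolled: "The sequence and duration of medication and behavioral interventions will vary by patient and site". It then says the trial will record which medications are used and "will include as covariates when and how medications change between the 4-month surveys". No outcome, model or analysis tier is attached to that commitment.

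The Abstract (Methods/design) describes the mixed-effects model for the primary and secondary outcomes "with baseline scores functioning as covariates, treatment condition as a between-subject factor", with outcomes at six time points. It has no medication term.

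Under Data analysis, the paragraph on intention-to-treat and noncompliance takes assignment as the basis of the standard comparison: "Standard intention-to-treat (ITT) estimates the average treatment effect by comparing outcomes based on assignment to treatment". As-treated, per-protocol and complier-average analyses are added alongside it.

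Three statements bear on whether A-CHESS could alter medication:

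- Among the secondary hypotheses is "greater retention in treatment" (Study design, hypotheses, and outcomes).
- The description of the A-CHESS services says "The coaches encourage individuals to follow up with their health care providers/prescribers regarding medication-assisted treatment questions".
- The same description covers a dashboard and alerts that may lead a counsellor to intervene with a patient at risk.

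**The concern.** Allocation is random ("randomize participants in a 1:1 ratio"), so a comparison by arm, with or without covariates fixed before randomisation, estimates the effect of assignment. A medication change between two follow-up surveys is not fixed before randomisation. Conditioning on it can distort the comparison in three ways:

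- If A-CHESS alters medication and medication alters opioid use, adjustment takes that route out of the estimated effect.
- If A-CHESS alters medication, and unmeasured severity drives both medication change and opioid use, patients with the same medication history are no longer comparable between arms. This adds bias of its own.
- If opioid use triggers medication change, the covariate is partly a consequence of the outcome. Adjusting for it then absorbs some of the effect, even if A-CHESS has no direct influence on prescribing.

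At stake is whether the reported coefficient for percentage of days using illicit opioids is the intention-to-treat effect. Because the article can be read two ways, the choice between two different estimates could also be left until data are in hand.

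**Working it through.** **1. The passages side by side.** The Control condition section commits to post-randomisation medication covariates and does not say where. The Abstract's model has baseline scores only. The intention-to-treat paragraph makes assignment the basis of the standard comparison. The last two fit together. The first fits them only if its covariates stay out of the intention-to-treat models, which the article does not say.

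**2. The plan's own figure.** 440 × (1 − 0.35) = 286, as stated, or 143 per arm. A simple two-sample calculation at a standardised difference of 0.35, with two-sided alpha 0.05 (assumed), gives 84.1% power. The article's 80% comes from a longitudinal power program whose correlation inputs are not given. That figure is not in dispute; the 84.1% is only a reference for step 4.

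**3. The arithmetic of adjustment.** Let *a* be the amount by which A-CHESS lowers the probability of a medication change, and *b* the amount by which a change raises the outcome. With no shared cause of change and outcome:

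adjusted effect = total effect + *a* × *b*

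Assumed inputs, none from the documents: 30% of control patients have a change, every change is adverse, *b* = 0.5 on a scale where the control SD is about 1, and the total effect is −0.35.

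- *a* = 0: −0.35 + 0 = −0.35
- *a* = 0.05: −0.35 + 0.025 = −0.325
- *a* = 0.10: −0.35 + 0.05 = −0.30
- *a* = 0.20: −0.35 + 0.10 = −0.25
- *a* = −0.10 (A-CHESS prompts more changes): −0.35 − 0.05 = −0.40

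**4. Adding an unmeasured severity factor.** Simulation with at least 1,000,000 patients per scenario and ordinary least squares. Severity raises the outcome by 0.5 per SD and the log-odds of a change by 1.0 per SD. Adding it moves the control rate to about 33% and the reductions slightly above the nominal values.

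| Nominal reduction in changes | Adjusted, no severity factor | Adjusted, with severity factor | Approximate power at 143 per arm |
|---|---|---|---|
| 0 points | −0.35 | −0.35 | 84% |
| 5 points | −0.33 | −0.31 | 79% to 73% |
| 10 points | −0.30 | −0.25 | 72% to 57% |
| 20 points | −0.25 | −0.16 | 57% to 28% |

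Without the medication covariate, the estimate stays near −0.35 in every row.

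**5. In days.** The article equates 0.35 with about three use days per month, which implies an SD of about 3 / 0.35 = 8.6 days. So −0.33, −0.25 and −0.16 correspond to about 2.8, 2.1 and 1.4 days per month.

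**6. Use driving medication.** Suppose A-CHESS has no direct effect on medication, but the log-odds of a change rise by 0.4 to 1.2 per SD of opioid use (assumed). Adjustment then takes a true 0.35 to roughly 0.34 to 0.29. This loss is smaller, but it needs only that A-CHESS reduces use and that use influences prescribing.

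**The case against.** The strongest reply is that the article never says the primary model contains these covariates. The sentence on medication names no model, the only model description lists none, and the as-treated and per-protocol analyses are a natural home for them. This stands. A reader might infer that the primary analysis will adjust for medication changes and will therefore lose part of the A-CHESS effect. The documents support neither step as fact. What remains is an unrestricted commitment that conflicts with the stated model if applied there.

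It can also be said that an effect of A-CHESS on medication is not claimed. Medication change is not among the named mediators, retention is measured by appointments attended, and the sentence about coaches may simply mark the limit of their role. This too is fair: the link is plausible, not stated. Step 6 shows that some distortion can arise without a direct link, provided use drives prescribing.

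The illustration treats every change as harmful, whereas care is tailored to the patient and a change may help. It also omits the baseline score, which would absorb some of the severity factor. The figures therefore show sensitivity; they do not forecast the bias.

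Finally, a reader might infer from the Abstract that the model leaves out the randomisation factors ("stratifying on gender and site and balancing on age, level of care", and prior treatment). That does not follow. An abstract in a condensed article need not carry the full covariate list, nothing says these factors are excluded, and leaving them out of a linear model would mainly cost precision without biasing the comparison.

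**Conclusion.** The point holds in a limited form. The protocol article commits, without restriction, to adjusting for events after randomisation that A-CHESS or opioid use could plausibly alter. If that commitment is carried into the primary or secondary outcome models, the coefficient may cease to be the effect of assignment that the article takes as its standard.

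The size and sign of the departure rest on effects the documents do not give. Under the assumptions above, it ranges from nothing, through shrinkage of 0.35 to between 0.33 and 0.16, to inflation (0.40 in the example) if A-CHESS prompts more changes. It would be small if neither A-CHESS nor its effect on use alters medication. That the effect will be reduced, or by a particular percentage, cannot be concluded. The mismatch between the Control condition section and the Abstract's model depends on no assumption and should be resolved before outcome data are analysed.

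**What to change.** Replace the covariate commitment under Control condition: MAT with wording to this effect: the models that estimate the intention-to-treat effect on primary and secondary outcomes use only covariates fixed before randomisation, of which medication type at baseline may be one; medication changes after randomisation are reported by arm and enter only analyses labelled as mediation, sensitivity, as-treated or per-protocol. This brings the section into line with the Abstract's model and the intention-to-treat paragraph, and keeps the medication data in use where they are informative.

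The cost is a change of wording. No new data are needed, since the article already commits to documenting medications. The downside is that any precision gained from a time-varying medication covariate is given up in the main models.
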